## Abstract

**Background:**

Self-reported penicillin allergies are highly prevalent in hospitalised patients and are associated with poor health and health service outcomes. Critically ill patients have historically been underrepresented in prospective delabelling studies in part due to concerns around clinical stability and reliability of penicillin skin testing. Allergy assessment tools exist to identify low-risk penicillin allergy phenotypes and facilitate direct oral challenge delabelling. PEN-FAST is a clinical decision rule that has been validated to predict true penicillin allergy in a cohort of non-critically ill patients. There is however limited evidence regarding the feasibility, safety and efficacy of direct oral challenges and the use of delabelling clinical decisions rules in the intensive care setting.

**Methods:**

Critically ill patients in the intensive care unit (ICU) with low-risk penicillin allergy phenotypes (PEN-FAST score < 3) will be randomised 1:1 to direct oral penicillin challenge (single dose 250 mg oral amoxicillin or implicated penicillin) or routine care, followed by a 2-h observation period. Patients will receive a second oral challenge/observation prior to hospital discharge (with subsequent observation for 2 h). An assessment for antibiotic-associated adverse events will also be undertaken at 24 h and 5 days post each challenge/observation and again at 90 days post-randomisation. The primary outcome measures are feasibility (proportion of eligible patients recruited and protocol compliance) and safety (proportion of patients who experience an antibiotic-associated immune-mediated adverse event or serious adverse event).

**Discussion:**

We will report the feasibility and safety of point-of-care penicillin direct oral challenge in this first randomised controlled trial of low-risk penicillin allergy in critically ill hospitalised patients. Upon completion of the project, important findings will inform the design of planned large prospective multi-centre clinical trials in Australian and international ICUs, further examining safety and efficacy and exploring antimicrobial prescribing-related outcomes following penicillin oral challenge.

**Trial registration:**

Australian New Zealand Clinical Trials Registry

Registration Number: ACTRN12621000051842

Date registered: 20/01/2021

https://www.anzctr.org.au/Trial/Registration/TrialReview.aspx?id=379735&isReview=true

**Supplementary Information:**

The online version contains supplementary material available at 10.1186/s40814-023-01337-8.

## Background

Patient-reported penicillin allergies result in poor health outcomes for patients and drive inappropriate antibiotic prescribing, antimicrobial resistance and healthcare costs [1–5]. Critically ill patients, such as those in the intensive care unit (ICU), are especially vulnerable to the impact of penicillin allergies [6, 7], yet have been underrepresented in interventional prospective delabelling (i.e. the removal of a patient’s antibiotic allergy history (“label”) via testing or medical record reconciliation [8]) programmes [9]. This impact is magnified, as the prevalence of penicillin allergies is highest in the critical care setting (9–15%) [1], with 50% of these considered low risk and amenable to point-of-care delabelling [3]. Despite the described burden of low-risk penicillin antibiotic allergies being highest in the ICU setting, these have not been addressed in controlled interventional studies.

We recently demonstrated in an Australian ICU that antibiotic allergies are associated with inferior prescribing, in particular the excessive utilisation of vancomycin (aOR 2.04; 95% CI 1.07, 3.86) and inadequate use of narrow spectrum beta-lactams (aOR 0.52; 95% CI 0.29, 0.94) [5]. In a range of observational studies that have included ICU patients, penicillin allergies are associated with the increased use of restricted antibiotics [5].

Our previous work has shown that more than 85% of penicillin allergies can be removed by formal skin prick allergy testing [10], and 96–98% with low-risk allergies can be removed by point-of-care oral challenge (i.e. test dose in non-ICU hospitalised patients) [11, 12]. However, the safety and efficacy of oral challenge in critical care are ill-defined [5]. In a recent systematic review, Moran et al. identified that penicillin allergy testing in the ICU was associated with increased use of narrow-spectrum antibiotics and decreased utilisation of restricted antimicrobials [5]. In addition, in a single-centre study, narrow-spectrum beta-lactams were utilised in 39.5% of ICU patients reporting any antibiotic allergy compared with 58.8% without (*p* = 0.028) [6].

Traditional penicillin allergy skin testing in the ICU has challenges, including the potential for false negatives, resourcing requirements and time pressures [5].

As an alternative to traditional assessment, we have validated the use of an antibiotic allergy assessment tool and point-of-care direct oral challenge in non-critically ill hospitalised inpatients (*n* = 196, 98.9% efficacy) [12]. Further, a recent unmatched single-centre cohort study demonstrated the safe administration of single-dose direct amoxicillin challenge in ICU patients with low-risk penicillin allergy (*n* = 54, 100% uncomplicated) [13]. Finally, our group has internally and externally validated a novel penicillin allergy clinician decision rule (PEN-FAST) that is able to identify low-risk penicillin allergies with a negative predictive value (NPV) of 96% (95% CI 94–98%) for a score of < 3 [14]. Therefore, whilst validated tools exist to enable inpatient penicillin assessment and delabelling, limited evidence is available regarding the safety and efficacy in the ICU setting.

## Methods/design

### Study objectives

To investigate the feasibility and safety of a direct oral penicillin challenge in adult ICU patients that have a low-risk penicillin allergy (PEN-FAST score < 3). Outcome measures are listed in Table 1 and include the primary outcomes of safety and feasibility of direct oral challenge. Secondary outcomes include proportion of allergy labels removed post-oral challenge, proportion of positive repeat oral challenges, pre- and post-randomisation antimicrobial utilisation, in-hospital and 30-day mortality and length of stay.

**Table 1 Tab1:** Outcome measures

**Primary outcome measures**	
* Feasibility outcome measures*	
* Eligibility to screened ratio*	Proportion of patients that are eligible for intervention
*** Recruitment to eligibility ratio***	Proportion of eligible patients consenting to the participation in the study *(a ratio of* ≥ *50% will be used as the primary determinant of feasibility)*
* Intervention to recruitment ratio*	Proportion of patients randomised to the intervention arm that had the intervention delivered as per protocol
* Protocol compliance*	Proportion of randomised patients that complete all study activities as per protocol
* Safety outcome measures*	
* Safety*	Proportion of patients with a penicillin allergy who experience an antibiotic-associated immune-mediated adverse event OR serious adverse event *(a proportion of* < *5% will be used as the determinant of safety)*

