**Exploratory outcome measures**	
◦ *Proportion of participants in the intervention arm successfully delabelled post oral challenge* ◦ *Proportion of participants in the intervention arm with positive repeat oral challenge (post-ICU discharge)* ◦ *Utilisation of any penicillin during hospital admission* ◦ *Utilisation of any narrow-spectrum beta-lactam during hospital admission* ◦ *Utilisation of vancomycin during hospital admission* ◦ *Utilisation of any restricted antibiotic during hospital admission* ◦ *In-Hhspital and 30-day mortality* ◦ *ICU length of stay and hospital length of stay*	

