### Statistical methods

Data analysis will be performed on an intention-to-treat basis as well as per protocol. Summary statistics will be used to describe the clinical data and presented as mean ± standard deviation (SD), median with interquartile range (IQR) or percentages as appropriate.

Feasibility and safety outcomes will be reported as percentage with 95% confidence intervals. Logistic regression will be used to compare antibiotic utilisation and mortality between groups. Results will be reported as odds ratios with 95% confidence intervals. Negative binomial regression will be used for comparison of length of stay (reported as incidence rate ratio with 95% CI). Results will be reported according to CONSORT guidelines [17].

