#### Harms

Serious adverse events (SAEs) will be defined as any adverse drug event that, in the opinion of the investigators, is causal for any of these outcomes: (1) death; (2) life-threatening reaction; (3) inpatient hospitalisation; (4) results in persistent or significant disability/incapacity; (5) congenital anomaly or birth defect; or (6) requires intervention to prevent permanent impairment or damage. SAEs that occur from the time of commencement of study treatment to 5 days after the second challenge/observation will be collected and reported to the approving ethics committee within 24 h of study staff becoming aware of the event.

An antibiotic-associated immune-mediated adverse event will include any immune-mediated reaction within 48 h of an antibiotic dose judged by two independent reviewers. An antibiotic-associated adverse event will be defined as any non-immune mediated reaction (e.g. diarrhoea, nausea and vomiting) within 48 h of an antibiotic dose judged by two independent reviewers.

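### The <5% safety rule names no arm, so as written its denominator includes the 40 controls who are never challenged

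*Protocol article*

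**What the plan says.** The Study objectives section gives the aim: "To investigate the feasibility and safety of a direct oral penicillin challenge in adult ICU patients" whose allergy is low risk. Table 1 defines the primary safety outcome as "Proportion of patients with a penicillin allergy who experience an antibiotic-associated immune-mediated adverse event OR serious adverse event" and adds that a proportion below "5% will be used as the determinant of safety". The Methods part of the Abstract gives the same outcome, again without an arm. The Statistical methods section says: "Feasibility and safety outcomes will be reported as percentage with 95% confidence intervals".

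Other rows of Table 1 do name the arm when one arm is meant. A feasibility row reads "Proportion of patients randomised to the intervention arm that had the intervention delivered as per protocol", and an exploratory row reads "Proportion of participants in the intervention arm successfully delabelled post oral challenge".

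Under Design and schedule and Sample size, 80 patients with a low-risk penicillin allergy are allocated 1:1, 40 per arm. Under Control, the control arm has routine management with no challenge, but the same schedule of observations and adverse event review. Under Harms, the immune-mediated component covers reactions within 48 h of any antibiotic dose, judged by two independent reviewers. A serious adverse event is "any adverse drug event that, in the opinion of the investigators, is causal for any of these outcomes" that follow in a list.

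**The concern.** The objective concerns patients who are challenged, while the decision rule is defined over a group that everyone in the trial belongs to. If the rule is followed literally, half the denominator was never exposed to the challenge, and an excess in the intervention arm is roughly halved before it meets the 5% limit. Safety is one of the two primary questions, and the results are meant to inform larger trials. The two readings also tolerate different numbers of events. In an open-label trial, the choice between them should not remain open once events are known.

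**Working it through.** **Inputs from the protocol.** 80 patients, 40 per arm (Design and schedule; Sample size). Limit: observed proportion below 5% (Table 1). PEN-FAST negative predictive value 96%, 95% CI 94 to 98%, for a score below 3 (Background), from a cohort that was not critically ill (Abstract). This implies a true allergy risk of about 1 − 0.96 = 4% (2 to 6%).

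**The plan's own figure.** The Sample size section takes 200 eligible × 0.50 recruited × 0.85 completing = 85, which reproduces and supports 80 enrolments. It is a recruitment projection; no calculation is given for the 5% safety rule.

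**Events tolerated.**
- Denominator 80: 3/80 = 3.75% passes; 4/80 = 5.0% does not. Exact 95% CI for 3/80: 0.8 to 10.6%.
- Denominator 40: 1/40 = 2.5% passes; 2/40 = 5.0% does not. Exact 95% CI for 1/40: 0.1 to 13.2%.
- If all 3 tolerated events are in the intervention arm: 3/40 = 7.5%, exact 95% CI 1.6 to 20.4%.
- If only 85% of the arm were dosed, 40 × 0.85 = 34, the limit is still 1 event (1/34 = 2.9%; 2/34 = 5.9%).

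**Probability of passing, no control events (assumed).** With no control events, all events come from X ~ Binomial(40, p). The pooled rule passes if X ≤ 3 and the arm-only rule if X ≤ 1. At p = 0.075, P(X = 0), P(1), P(2), P(3) are 0.044, 0.143, 0.227 and 0.233. So P(X ≤ 1) = 0.188 and P(X ≤ 3) = 0.647.

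| True intervention-arm risk | Pooled rule (≤3/80) | Intervention arm only (≤1/40) |
|---|---|---|
| 2% | 99% | 81% |
| 4% | 93% | 52% |
| 5% | 86% | 40% |
| 7.5% | 65% | 19% |
| 10% | 42% | 8% |
| 15% | 13% | 1% |

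**Relaxing the zero-control assumption.** The protocol gives no control event rate. With 7.5% in the intervention arm, control rates of 2%, 5% and 10% (assumed) bring the pooled pass probability to 47%, 26% and 7%, against 19% for the intervention arm alone. The leniency of pooling shrinks as control events rise, and at 10% it reverses.

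**Background events with a harmless challenge.** If other antibiotics or drugs cause events in 2%, 5% or 10% of patients in both arms (assumed), the pooled rule passes 92%, 43% or 4% of the time and the arm-only rule 81%, 40% or 8%. Changing the denominator does not remove this effect. Separate reporting of the controls is what shows the background.

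**Limit of 40 patients.** With 0/40, the exact 95% upper limit is 1 − 0.025^(1/40) = 8.8%, so even no events would not exclude 5%.

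**The case against.** The strongest reply is that pooling is never stated. The sentence introducing Table 1 speaks of the safety of direct oral challenge, and percentages by arm would fit the Statistical methods section equally well. An analysis plan that is not shown may well report by arm. This stands as far as it goes: pooling is the plain reading, reinforced by neighbouring rows that name the arm, but not an explicit instruction. It does not remove the point, because Table 1 fixes one proportion and one cut-off, and reporting by arm would not say which proportion the cut-off applies to.

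Three stronger readings are tempting and are not supported.
- A reader might infer that counting reactions to any antibiotic, and serious events from any drug, is an error. It is a defensible choice: it captures harm from later penicillin use after delabelling, and adjudication and the 48 h window limit the immune-mediated component. Replacing it with events attributed to the challenge would make an open-label primary outcome depend on attribution, with no counterpart in controls.
- A reader might infer that undosed patients in the intention-to-treat set go unaddressed. The Statistical methods section also plans a per-protocol analysis, although that does not settle which arm is counted.
- A reader might infer that a formal between-arm safety test is missing. In a pilot of 40 per arm that reports estimates with confidence intervals, its absence is not in itself an error.

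It is also fair to say that 7.5% and 10% exceed the risk suggested by the protocol's own sources. At 4%, which is inside the limit, the arm-only rule fails an acceptable challenge about 48% of the time. That is a real cost of the fix.

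**Conclusion.** The point holds as a badly fixed primary criterion: the denominator of the <5% rule does not match the objective. As written, it tolerates 3 events in 80 even when the intervention arm shows 7.5%. At a true intervention-arm risk of 7.5% it passes 65% of the time against 19% on that arm alone, and at 10%, 42% against 8%. These figures rest on reading the row as covering both arms, on 40 patients per arm, and on no control events, which is an assumption. The documents do not support saying that the trial will certainly pool, or that the composite itself is wrong.

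**What to change.** In Table 1 and the Abstract, state that the <5% criterion applies to intervention-arm participants who received at least one challenge dose. Keep the existing adjudicated composite as the numerator. Report it separately for each arm with 95% confidence intervals, so that control events show the background from other antibiotics and drugs; a descriptive risk difference is optional. Events adjudicated as related to a challenge dose can be a supporting analysis.

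The main result needs only a change of wording, since events are already collected in both arms; the supporting analysis would also need relatedness to the challenge recorded at the planned adjudication. The cost is in the operating characteristics. With about 40 challenged patients the rule tolerates 1 event instead of 3, and passes about 81% of the time at a true 2% risk and 52% at 4%. The protocol should say so and describe 5% as a pilot benchmark, not as a demonstration that the risk is below 5%.

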### Sample size

This is a pilot study designed to assess the feasibility and safety of the ICU oral challenge programme, as well as providing local estimates for subsequent power calculation for future trials.

With regard to the feasibility of penicillin allergy assessment within the ICU, we assume that 9% of all screened patients will report a penicillin allergy as per national data [1], and in an observational study by Moran et al. in Austin Health ICU [6], 200 patients would be expected to be eligible in a 12-month study period. Assuming 50% recruitment and that 85% complete the randomised challenge/observation, this would generate a projected potential pool of 85 eligible participants in 1 year. As such, a total of 80 enrolments and 1:1 randomisation (40 in each arm) are planned.

Whilst the above assumptions may be true (particularly for the primary study site, with an established clinical and research antibiotic allergy service), there are anticipated factors which may limit recruitment. The expected number of 200 eligible patients was calculated from a single tertiary ICU, and the different patient populations of other ICUs may vary the number of eligible patients. Temporary disruptions are expected due to the ongoing SARSCo-V2 pandemic, with altered patient flow through ICUs and investigator availability. Delays in activating study sites may slow recruitment and consistent recruitment may be more challenging at sites with less robust allergy research services.

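### The single pooled <5% safety criterion counts a fatal reaction and a non-serious one alike, names no denominator, and leaves serious events without a criterion of their own

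*Protocol article*

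**What the plan says.** The safety row of Table 1 (Primary outcome measures) defines one outcome: "Proportion of patients with a penicillin allergy who" "experience an antibiotic-associated immune-mediated adverse event OR serious adverse event". It attaches one rule, that a proportion under 5% "will be used as the determinant of safety". The row names no arm.

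The Harms section defines the two components. The immune-mediated component is "any immune-mediated reaction within 48 h of an antibiotic dose judged by two independent reviewers", with no grade or severity threshold. The serious component covers adverse drug events that the investigators judge to have caused one of six listed outcomes, among them death and a life-threatening reaction.

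On size, the Sample size section says "a total of 80 enrolments and 1:1 randomisation (40 in each arm) are planned". Statistical methods adds that safety outcomes are given as percentages with 95% confidence intervals. Data monitoring provides for two independent adjudicators and no data monitoring committee. In-hospital and 30-day mortality appear only among the exploratory outcomes.

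**The concern.** Each affected patient adds one to the same numerator, whether the event is a transient rash or a drug-caused death, and one cut-off then decides whether the challenge is called safe. Two consequences follow.

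First, serious harm has no criterion of its own. At this sample size a single serious event is too small a percentage to breach 5%, so the stated rule returns a favourable answer.

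Second, a non-serious immune-mediated reaction to the challenge is also a positive test, and the protocol's Background leads one to expect some. It reports that "96–98% with low-risk allergies can be removed by point-of-care oral challenge" and that the PEN-FAST rule is "able to identify low-risk penicillin allergies with a negative predictive value (NPV) of 96"%. The 5% line therefore lies close to the yield that some of the cited sources imply, and a few non-serious positives could produce an unfavourable safety verdict.

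The trial is meant to inform larger multi-centre trials, so a verdict that misleads in either direction would feed into that decision.

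**Working it through.** **Inputs.** Planned size 80, 40 per arm; 200 eligible patients a year, 50% recruited, 85% completing (Sample size). Rule: observed proportion strictly below 5% (Table 1). Rates of label removal or correct low-risk classification: 96–98%, 96% and 98.9% (Background).

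**The plan's own figure.** 200 × 0.50 × 0.85 = 85, as stated, from which 80 enrolments are planned; 80/2 = 40 per arm. The 5% safety rule has no stated power or precision basis to reproduce.

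**What the rule does, by denominator** (exact Clopper-Pearson 95% intervals):

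| Denominator | Most events that pass | Fewest events that fail |
|---|---|---|
| 40 (intervention arm) | 1/40 = 2.5% (0.06% to 13.2%) | 2/40 = 5.0% (0.6% to 16.9%) |
| 34 (85% of 40 complete) | 1/34 = 2.9% (0.07% to 15.3%) | 2/34 = 5.9% (0.7% to 19.7%) |
| 80 (all participants) | 3/80 = 3.75% (0.8% to 10.6%) | 4/80 = 5.0% (1.4% to 12.3%) |

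Severity does not enter any cell. The passing events may all be fatal and the failing events may all be non-serious.

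**Chance that non-serious reactions alone fail the rule, judged in the 40 challenged patients.** Assume every label not removed, or wrongly classed as low risk, is a non-serious immune-mediated reaction. Then p = 1 − 0.989 = 1.1%, 1 − 0.98 = 2%, or 1 − 0.96 = 4%. The rule fails at two or more events:

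P(X ≥ 2) = 1 − (1 − p)^40 − 40p(1 − p)^39

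- p = 1.1%: 1 − 0.642 − 0.286 = 0.072, about 7%.
- p = 2%: 1 − 0.446 − 0.364 = 0.190, about 19%.
- p = 4%: 1 − 0.195 − 0.326 = 0.479, about 48%.

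**The same, judged over all 80.** If reactions arise only among the 40 challenged, failing needs four or more events in those 40. P(X ≥ 4) is 0.1% at p = 1.1%, 0.8% at 2% and 7.5% at 4%. Control-arm reactions to other antibiotics would raise these figures.

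The unnamed denominator thus moves the chance of failing, at a 4% rate, from 48% to 7.5%.

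**The case against.** The strongest reply has four parts.

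*Including non-serious reactions is cautious, not wrong.* An immune-mediated reaction provoked in an ICU patient is a real harm, and Harms counts reactions after any antibiotic dose, in either arm. This stands. A reader might infer that the composite mainly measures how many tested patients are truly allergic. The documents do not support that: the definition is wider than the challenge dose, and test yield has its own exploratory outcomes (proportion delabelled, positive repeat challenge).

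*The false-alarm risk depends on chosen inputs.* This stands in part. A reader might take 19% to 48% as the risk. Background also gives 98.9% efficacy in 196 non-critically ill inpatients (about 7% risk) and an ICU cohort of 54 with no complicated challenge. None of the three rates used comes from ICU patients. Nor does the protocol say that every label not removed was an immune-mediated reaction. Likewise, that two mild reactions fail the rule is true only with 40 or fewer patients in the denominator; over 80 they are 2.5% and pass.

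*Other safeguards exist.* Events are adjudicated by two independent clinicians, serious events go to the ethics committee within 24 h, and the confidence interval around 1/40 reaches about 13%, which shows how little 2.5% establishes. These protect patients and readers, but none alters the stated rule. Component tables may well be in the full protocol or analysis plan; their absence from the article is not the point made here.

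*It is a pilot, and any unweighted composite behaves this way.* The 5% figure is not tied to a hypothesis test or a stopping rule, which limits the weight of the point. It remains the only safety criterion that the article states.

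**Conclusion.** The point holds in a limited form. As written, the determinant would be met despite one fatal or life-threatening reaction in 40 (2.5%), or up to three serious events in 80 (3.75%), and would not be met with two non-serious reactions in 40 or four in 80 (5.0%). This follows from the definitions and needs no assumption beyond the choice of denominator, which Table 1 leaves open.

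The chance that non-serious reactions alone cause a failure is less certain. It is about 7%, 19% or 48% at rates of 1.1%, 2% or 4%, provided that the denominator is the 40 challenged patients, that all reactions are non-serious, and that rates from patients outside ICU or not critically ill carry over.

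It would be tempting to conclude that the endpoint is invalid or that the investigators would report a death as safe. The documents support neither. The pooled endpoint is defensible; the weakness is that it alone decides safety. This is a worthwhile, low-cost improvement, not a defect that invalidates the trial.

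**What to change.** Amend the safety row of Table 1, and Statistical methods to match:

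1. Keep the composite and its 5% benchmark, name the arm in which the benchmark is judged, and state that the composite does not decide safety alone.
2. Add adjudicated serious events as a separate primary safety component, reported by arm as count, percentage and exact 95% CI.
3. State in advance that safety will not be concluded from the pooled percentage if a serious challenge-related event occurs.
4. Report non-serious immune-mediated reactions separately.

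The 5% benchmark stays, so a few non-serious reactions can still exceed it. Separate reporting then shows that the excess came from non-serious events.

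The cost is wording only; no extra patients or data are needed. The downside is two safety statements in place of one and a slightly stricter route to a conclusion of safety.

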#### Data monitoring

As a pilot study with a small number of planned participants utilising an established safe allergy assessment protocol, a data monitoring committee will not be established. Any serious adverse events or antibiotic-associated immune-mediated adverse events will be referred to two independent clinicians with extensive experience in antibiotic allergy for adjudication.

Participant retention will be promoted through the offer of telephone follow-up for patients post-hospital discharge.

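### The below-5% safety criterion is a bare point-estimate cut with no stated denominator; among about 40 challenged patients no passing result excludes a true rate of 5%

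*Protocol article*

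**What the plan says.** Table 1 lists safety among the primary outcomes. The measure is "Proportion of patients with a penicillin allergy who experience an antibiotic-associated immune-mediated adverse event OR serious adverse event", and a proportion of less than "5% will be used as the determinant of safety". The row names no arm. Other rows do: the intervention-to-recruitment ratio and the delabelling and repeat-challenge items are each confined to the intervention arm.

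Statistical methods says that safety will be reported as a percentage with a 95% confidence interval, by intention to treat and per protocol. It does not say that the interval has any part in the safety verdict.

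Sample size derives the number of patients from recruitment: "200 patients would be expected to be eligible in a 12-month study period", followed by "Assuming 50% recruitment and that 85% complete the randomised challenge/observation". It concludes that "a total of 80 enrolments and 1:1 randomisation (40 in each arm) are planned". It gives no safety event rate, precision or error rate.

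Background cites several figures that bear on a plausible rate, among them "a negative predictive value (NPV) of 96" per cent for a PEN-FAST score below 3. It labels none of them as the rate expected in this trial.

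**The concern.** The article fixes both a yes-or-no safety criterion and a sample size, and the two were not set with each other in view. A cut applied to an observed proportion in a few dozen patients allows only one or two event counts to pass. Even the best of these may be compatible with rates well above the cut. Because the denominator is not named, the number of events that passes is also open: the same trial could pass on one reading and fail on the other.

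At stake is what the trial may conclude on a primary outcome. As written, 0 or 1 event yields a finding of safety that the data could not support as a statement about the true rate. Conversely, 2 events in 40 yield a finding of not safe that chance alone could produce at a rate below the cut.

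**Working it through.** **The plan's own figure.** 200 eligible × 0.50 recruited × 0.85 completing = 85. This reproduces the stated annual pool, from which 80 (40 per arm) follows. It is a recruitment projection; there is no safety calculation to reproduce.

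**Inputs.** Cut: observed proportion below 5% (Table 1). Denominator: 40 (one arm), 34 (85% of 40, if the completion assumption is applied to the challenged arm) or 80 (both arms), all from Sample size.

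**Which counts pass.**
- n = 40: 1/40 = 2.5% passes; 2/40 = 5.0% is not below 5% and fails.
- n = 34: 1/34 = 2.9% passes; 2/34 = 5.9% fails.
- n = 80: 3/80 = 3.75% passes; 4/80 = 5.0% fails.

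**Exact (Clopper-Pearson) two-sided 95% upper limits.** For zero events the limit is 1 − 0.025^(1/n). For x events it is the p that solves P(X ≤ x | n, p) = 0.025.
- 0/40: 1 − 0.025^(1/40) = 8.8%. 1/40: 13.2%.
- 0/34: 1 − 0.025^(1/34) = 10.3%. 1/34: 15.3%.
- 0/80: 1 − 0.025^(1/80) = 4.5%. 1/80, 2/80 and 3/80: 6.8%, 8.7% and 10.6%.

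The choice of interval does not alter the result at 0/40: Wilson also gives 8.8%, and a one-sided 95% limit is 1 − 0.05^(1/40) = 7.2%. With zero events, the smallest n whose limit falls below 5% is 72 (two-sided) or 59 (one-sided).

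**Probability of passing.** For n = 40 this is (1 − p)^40 + 40p(1 − p)^39. At p = 0.05 it is 0.1285 + 0.2706 = 0.399. For n = 80 it is P(X ≤ 3).

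| True rate | n = 40 (≤ 1 event) | n = 34 (≤ 1 event) | n = 80 (≤ 3 events) |
|---|---|---|---|
| 1.1% | 93% | 95% | 99% |
| 2% | 81% | 85% | 92% |
| 4% | 52% | 60% | 60% |
| 5% | 40% | 49% | 43% |
| 6% | 30% | 39% | 29% |
| 8% | 16% | 23% | 11% |
| 10% | 8% | 13% | 4% |

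**Rates that the Background implies.** These are inferences that assume a true allergy shows as an event.
- PEN-FAST NPV of 96% (95% CI 94–98%): 4%, range 2–6%.
- 96–98% of low-risk labels removed by oral challenge outside ICU: 2–4%.
- 98.9% efficacy in 196 non-critically ill inpatients: 1.1%.
- ICU cohort: 0/54, with an exact upper limit of 1 − 0.025^(1/54) = 6.6%. This is already tighter than the best result possible on 40.

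Over 1.1–4% the pass probability on 40 patients is 93–52%. Over the NPV's interval of 2–6% it is 81–30%.

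**The case against.** The strongest reply is that this is a pilot, openly sized on recruitment, and that pilots may use simple progression thresholds. That stands: sizing on recruitment is not an error. The article also promises a 95% confidence interval, so a reader of 0/40 would see the wide range, and the choice of interval method is ordinarily left to the analysis plan. The Abstract and the Discussion speak of initial safety data with further study of safety to follow. A reader might infer that a pass would be carried into later trials as demonstrated safety; those passages do not support that.

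A reader might also infer that the challenge would pass only about half the time at the rate the plan itself expects. The plan states no expected rate. The 52% figure holds only at the 4% implied by the NPV; other figures in the same Background are lower and give up to 93%. Nor is 1 − NPV the endpoint. The composite counts immune-mediated reactions to any antibiotic and serious adverse drug events, so the true rate could lie on either side.

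Finally, a reader might say that no attainable result could ever show a rate below 5%. That is true for the challenged patients but not if all 80 are counted, since 0/80 has an upper limit of 4.5%. All 80 have a penicillin allergy and both arms receive the same adverse-event review, so the wording permits that reading.

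None of this ties the interval to the verdict, names the denominator or changes the role that Table 1 gives to the cut.

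**Conclusion.** The point holds as a moderate one. Table 1 attaches a safety verdict to an observed proportion, and the planned numbers cannot support that verdict as a statement about the true rate.

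The conclusion for the challenged patients needs no assumed event rate: both passing results, 0/40 and 1/40, leave 5% well inside the 95% interval, and a true rate at the limit passes 40% of the time. It does rest on taking the challenged arm as the denominator. That is the sensible reading because the stated objective is the safety of the oral challenge, and pooling would dilute challenge reactions with 40 unchallenged controls. On the pooled reading the defect shrinks but remains: of the four passing counts only 0/80 excludes 5%, and a true 5% rate still passes 43% of the time. Statements about how often the trial would pass at its likely rate are conditional on the rate assumed and should be given as a range.

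**What to change.** Change the wording of the safety row in Table 1 and add a short statement under Sample size or Statistical methods:

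- Keep the composite endpoint as defined in Table 1.
- Name the challenged patients as the denominator and report the control arm alongside.
- Describe the cut (at most 1 event in 40) as a progression signal, not as what decides safety.
- Print its pass probabilities over a range of true rates, for example 93%, 81%, 52%, 40%, 16% and 8% at 1.1%, 2%, 4%, 5%, 8% and 10%.
- Report the exact Clopper-Pearson 95% interval together with the verdict.
- State that even 0/40 leaves rates up to 8.8% open, so the trial will not conclude that the rate is below 5%.

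This leaves the cut, and so its power to discriminate, unchanged; what changes is the claim that rests on it. It needs no extra patients or staff. The cost is a more modest safety claim.
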